## Results

The primary aim of the study is to assess the effectiveness of the nurse-led TCG program in improving caregiver knowledge, readiness for discharge, and satisfaction with the care transition process. We anticipate that caregivers in the intervention group will show improved knowledge of CHD management, as indicated by higher scores on the CHDKS compared to caregivers in the control group. This improvement is expected to reflect the enhanced education provided through the TCG program, which includes pre-discharge education sessions and a personalized care guide.

Caregiver readiness for discharge is also expected to improve significantly in the intervention group. The readiness for discharge scale will measure how well caregivers feel prepared to manage the child’s care once at home. We hypothesize that caregivers in the intervention group will report higher levels of preparedness due to the additional support provided through the TCG program, which will include structured follow-up and the ability to address any questions or concerns during the post-discharge period.

Additionally, we expect caregiver satisfaction to be significantly higher in the intervention group compared to the control group. The caregiver satisfaction survey will measure satisfaction with the discharge process, the clarity of the information provided, and the level of support received. It is anticipated that caregivers who receive the nurse-led TCG will report greater satisfaction, as the program is designed to address their specific needs and provide continuous support after discharge.

Secondary outcomes will include increased caregiver confidence in managing key aspects of care, such as medication administration and recognizing emergency signs in their child. We expect that caregivers in the intervention group will report greater confidence in these areas, which could translate to a lower likelihood of post-discharge complications and fewer hospital readmissions. Hospital readmission rates and the number of complications within 30 days post-discharge will be tracked as secondary indicators of the effectiveness of the transition care intervention.

Overall, the study is expected to show that the nurse-led TCG program significantly improves caregiver outcomes in terms of knowledge, preparedness, confidence, and satisfaction. Furthermore, it is anticipated that this intervention will result in a reduction in post-discharge complications and hospital readmissions, indicating that better caregiver preparation leads to better child health outcomes during the transition from hospital to home.

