## Materials and methods

This study will have a mixed-methods design, incorporating both qualitative and quantitative approaches to address the research questions. The qualitative phase will involve focus group discussions (FGDs) with caregivers, nurses, and physicians to understand the challenges and unmet needs faced by caregivers during the transition of children with CHD from hospital to home. Multi-stakeholder opinion on transition care will help identify the gaps in caregiver preparedness and inform the development of the nurse-led TCG program. The qualitative data will be analyzed using thematic analysis, which will allow the identification of common themes and patterns in the experiences and challenges reported by the participants.

In the quantitative phase, a quasi-experimental design with a pre-test and post-test control group will be used to evaluate the effectiveness of the nurse-led TCG program. The intervention group will receive the TCG program, which will include pre-discharge education sessions, personalized discharge care guides, and telephonic follow-up support at specified intervals post-discharge. The control group will receive standard discharge instructions without the additional components of the TCG program.

The study will take place in the pediatric care units of a tertiary care hospital. The participants will include caregivers of children diagnosed with congenital heart disease who are preparing for discharge. Inclusion criteria will include caregivers who are the primary decision-makers and care providers for the child and caregivers of children with congenital heart disease who are scheduled for discharge from the pediatric care unit. Exclusion criteria will include caregivers who have limited language proficiency, caregivers who are unable to attend the intervention sessions, and caregivers who are unable to commit to the follow-up process due to logistical or other reasons.

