The primary outcome measures for this study will include caregiver knowledge of CHD and its management, caregiver readiness for discharge, and caregiver satisfaction with the transition process. Caregiver knowledge will be assessed using a congenital heart disease knowledge scale (CHDKS), which will be developed specifically for this study and validated for reliability and accuracy before data collection. Similarly, caregiver readiness for discharge will be evaluated using a readiness for discharge scale, which will be developed and subjected to rigorous validity and reliability testing. Caregiver satisfaction will be measured through a satisfaction survey assessing their experience with the discharge process, the information provided, and the support received; this tool will also undergo validity and reliability testing before implementation. All research instruments will be carefully developed and tested for content validity, construct validity, and reliability to ensure accurate and meaningful measurement of study outcomes.

Secondary outcomes will include caregiver confidence in managing care tasks, including medication administration and recognizing emergency signs in the child, as well as hospital readmission rates and post-discharge complications within 30 days of discharge. A caregiver confidence assessment tool will be developed specifically for this study and validated for reliability and accuracy before data collection. Hospital readmission rates and post-discharge complications will be tracked using hospital records and follow-up interviews. These outcomes will help assess the broader impact of the nurse-led TCG program on both caregiver preparedness and child health outcomes.

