Data collection will be conducted at three time points: baseline (at the time of admission), during discharge, and post-discharge follow-up (starting from seven days after discharge). At baseline (admission), caregiver surveys will be conducted to assess their initial knowledge, readiness, and confidence in managing care. During discharge, post-assessment will be carried out to evaluate changes in caregiver preparedness and understanding after receiving the nurse-led TCG. Post-discharge follow-up, starting from seven days after discharge, will involve caregiver surveys, telephone interviews, and a review of medical records to track hospital readmission rates and post-discharge complications up to 45 days after discharge. The qualitative data will be collected through FGDs, which will be audio-recorded, transcribed, and analyzed using thematic analysis. Quantitative data will be analyzed using statistical methods such as paired t-tests for comparing pre- and post-intervention measures, independent t-tests to compare the intervention and control groups, and multiple regression analysis to identify predictors of caregiver satisfaction and readiness for discharge.

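### The Results section reads fewer readmissions and complications as evidence that caregiver preparation improves child health, which a non-randomised comparison with no named adjustment cannot show

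*Protocol article*

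**What the plan says.** All places are in the Protocol article.

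- **Design (Materials and methods):** "a quasi-experimental design with a pre-test and post-test control group will be used to evaluate the effectiveness of the nurse-led TCG program". No randomisation and no method of forming the groups is described.
- **Outcomes:** readmission and complications are secondary. Materials and methods defines them as "hospital readmission rates and post-discharge complications within 30 days of discharge". Results says: "Hospital readmission rates and the number of complications within 30 days post-discharge will be tracked as secondary indicators". One is an event and the other a count.
- **Source of the data (Materials and methods):** "Hospital readmission rates and post-discharge complications will be tracked using hospital records and follow-up interviews". A review of medical records is part of follow-up.
- **Analysis (Materials and methods):** "Quantitative data will be analyzed using statistical methods such as paired t-tests for comparing pre- and post-intervention measures", then "independent t-tests to compare the intervention and control groups", then multiple regression to find predictors of satisfaction and readiness. No adjusted comparison of the two groups is named for any outcome.
- **Intervention (Materials and methods):** TCG combines education before discharge, a personalised care guide, and telephone support on days 7, 15, 30 and 45.
- **Interpretation (last paragraph of Results):** an anticipated reduction in complications and readmissions is described as "indicating that better caregiver preparation leads to better child health outcomes during the transition from hospital to home".

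**The concern.** The Results sentence moves in two steps from a group difference to a cause, and the design supports neither.

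The first step is from a difference between groups to an effect of TCG. Without randomisation, the groups may differ in how ill the children are. Adjustment for baseline severity would be the usual partial remedy, but the regression that is named serves another purpose.

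The second step is from an effect of TCG to an effect of caregiver preparation. TCG also provides continued telephone contact, which could influence child outcomes by itself. No analysis is named that relates caregiver knowledge, readiness or confidence to the child's events.

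At stake is the one claim in the article about children's health. The Discussion says that the findings will inform policymakers and hospital administrators. If the article were followed as written, a difference due to case mix could be presented to them as a benefit of preparing caregivers, or a real benefit could be masked.

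**Working it through.** The article gives no sample size, event rate or effect size, so there is no figure of its own to reproduce. Every rate, share and group size below is an assumption for illustration.

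**1. Crude risk ratio with no true effect**

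Let p be the share of severe cases in a group, k the risk ratio for severe against non-severe cases, and r the risk in non-severe cases. The group risk is r × (p·k + 1 − p). With no effect of TCG, r cancels:

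crude RR = (p_TCG·k + 1 − p_TCG) / (p_control·k + 1 − p_control)

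Assume p_TCG = 0.30 and p_control = 0.45.

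- k = 2: (0.60 + 0.70) / (0.90 + 0.55) = 1.30 / 1.45 = 0.897
- k = 3: (0.90 + 0.70) / (1.35 + 0.55) = 1.60 / 1.90 = 0.842

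These are apparent reductions of about 10% and 16% with no effect at all. With the imbalance reversed, the ratios are 1.45 / 1.30 = 1.115 and 1.90 / 1.60 = 1.188. In the first case a true ratio of 0.90 would appear as 0.90 × 1.115 = 1.00, so a benefit of that size would vanish.

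**2. How often a false reduction would reach significance**

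Assume a readmission risk of 20% in high-risk and 5% in low-risk children, and no true effect. The control rate with half the children at high risk, for example, is 0.50 × 20% + 0.50 × 5% = 12.5%. The last columns give the chance of a significant reduction in the TCG group at a two-sided 5% level, where 2.5% is nominal in that direction.

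| High-risk share, control vs TCG | Crude rates | RR | n = 50 per group | 100 | 200 | 500 |
|---|---|---|---|---|---|---|
| 50% vs 40% | 12.5% vs 11.0% | 0.88 | 4.2% | 5.1% | 6.8% | 11.1% |
| 50% vs 30% | 12.5% vs 9.5% | 0.76 | 6.9% | 10.0% | 15.8% | 32.8% |
| 60% vs 30% | 14.0% vs 9.5% | 0.68 | 10.3% | 16.5% | 28.6% | 59.9% |

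A larger study does not help: the false-positive rate rises with group size.

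**3. Does the t-test itself matter?**

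With no confounding, the simulated type I error of a two-sided 5% t-test was 0.028 to 0.054 on a yes/no outcome (30 to 100 per group, event rates 5% to 20%). On overdispersed counts (negative binomial, mean 0.3, size 0.5) it was 0.046 to 0.051. That is near nominal, or conservative when events are rare and groups small. The problem lies in the missing adjustment and not in the test.

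**4. Mechanism**

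No arithmetic applies here. Set side by side, the intervention has three components and the Results sentence credits one result of them, preparation. A comparison of all three together against standard discharge care cannot apportion the effect among them.

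**The case against.** Four points can be made in the article's defence.

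- **Test choice.** A reader might infer that the plan assigns a t-test to readmission and complications and has decided against adjusting for severity. The text does not support this. The methods are introduced as examples, the t-test is not tied to any outcome, and the model for a secondary event outcome may stand in a full protocol or analysis plan that is not shown. This stands: the absence of a model here is not in itself an error.
- **Strength of the claim.** A reader might infer that a lower rate is to be taken as proof. The sentence belongs to a paragraph of anticipated results and is not a decision rule. Earlier in Results the same link is put more cautiously, as something that could follow from greater confidence. This stands against the word proof. It does not remove the causal wording, which goes further than the article's own hedge and which a separate analysis plan would not correct.
- **Reporting.** A reader might infer that complications will be reported differently by group, because TCG teaches signs of deterioration. That is possible but not established. Both groups are contacted on the same days, controls are also told which emergency signs to watch for, and records are reviewed. Confirmation in records would not fully remove such a difference either, since caregivers who recognise illness sooner may also seek care sooner.
- **Assumed figures.** The imbalances and risks in the working come from no source in the article. This stands. They show that the problem can be material, not that it will occur.

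**Conclusion.** The concern holds for the causal conclusion. A difference in readmissions or complications between groups not described as randomised, compared by the one between-group method named, would not show that caregiver preparation improves child health. Under an assumed 30% against 45% severe disease and a two- to threefold risk, confounding alone gives a risk ratio of 0.90 to 0.84, and the reverse imbalance would hide a benefit of similar size. Even with confounding removed, the difference would belong to the TCG programme as a whole.

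The outcomes are secondary, so the primary comparisons of caregiver scores are not in question here. The size depends wholly on the assumed imbalance and on how strongly severity predicts events; the article gives neither.

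**What to change.** 1. Compare readmission (yes/no) and number of complications between groups by a risk or count regression adjusted for one or two baseline severity variables fixed in advance, such as CHD severity and surgery during this admission. Report ratios with 95% confidence intervals. The exact model family is a matter of preference.
2. Reword the closing sentence of Results along these lines: any difference in readmissions or complications will be reported as an adjusted association with the TCG programme as a whole, and as supportive evidence only.
3. As a sensitivity analysis, report complications confirmed in the medical records separately from those reported only by caregivers. The record review is already planned.
4. While editing, state the analysis window. Outcomes are defined at 30 days, but data collection is to "track hospital readmission rates and post-discharge complications up to 45 days after discharge".

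**Cost:** analysis text, a more modest conclusion and collection of one or two baseline variables, with no added participants or visits. Few events will limit how much can be adjusted for, confounders not measured will remain, and the intervals will be wide. For scale, detecting a true halving with 80% power at a two-sided 5% level needs 435 per group from an assumed 10%, 278 from 15% and 199 from 20%.

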## Discussion

This study protocol is designed to evaluate the effectiveness of the nurse-led TCG program in improving post-discharge care for children with CHD and their caregivers. The transition from hospital to home is a critical period for children with CHD, as caregivers often face challenges related to medication adherence, symptom management, emergency recognition, and access to healthcare services. Given the complexity of CHD care, structured interventions that provide comprehensive education, ongoing support, and timely follow-ups are essential in ensuring optimal child health outcomes and caregiver preparedness [8].

Existing literature underscores the significance of nurse-led interventions and structured caregiver education in pediatric populations. Studies have shown that organized discharge planning, follow-up support, and targeted caregiver training can significantly enhance caregiver confidence, reduce anxiety levels, and improve adherence to treatment regimens [9,10]. A systematic review highlighted that nurse-led educational programs focusing on chronic pediatric conditions resulted in better caregiver preparedness, reduced readmission rates, and improved overall child well-being [11]. Furthermore, structured caregiver training models have been linked to enhanced medication adherence and improved management of pediatric health conditions [12].

In addition to in-person training, nurse-led telephone follow-ups and remote support systems have been found to be highly effective in post-discharge care. For instance, a study demonstrated that telephonic follow-ups improved caregiver knowledge, decreased 14-day and 30-day hospital readmissions, and enhanced overall patient satisfaction [13]. Similarly, a randomized controlled trial (RCT) was conducted in Norway, where nurse-led post-discharge telephone support for cardiac surgery patients was associated with better self-management, reduced anxiety, and improved clinical outcomes [14]. These findings support the need for structured follow-up interventions to provide continuous support during the transition period.

Despite the growing evidence on the effectiveness of nurse-led interventions, limited research specifically addresses the unique needs of caregivers managing children with CHD. This study protocol seeks to bridge this gap by designing and testing the nurse-led TCG program, which integrates structured education, post-discharge follow-ups, and tailored support to empower caregivers in managing their child's condition at home [15]. The anticipated findings will contribute to the growing body of evidence on transition care models, reinforcing the need for multifaceted, nurse-led interventions that focus on caregiver empowerment, reduced hospital readmissions, and improved child health outcomes.

By systematically evaluating the impact of this intervention, this study aims to provide a robust evidence base for integrating nurse-led transition care models into routine pediatric CHD management. The findings will inform policymakers, healthcare professionals, and hospital administrators about the importance of structured discharge programs and their role in enhancing long-term pediatric outcomes.

## Conclusions

This study aims to evaluate the effectiveness of a nurse-led transition care guidance (TCG) program for caregivers of children with congenital heart disease (CHD). By utilizing a mixed-methods approach, the protocol focuses on improving caregiver knowledge, confidence, and satisfaction in managing the child's post-discharge care. The expected outcomes include enhanced caregiver preparedness, reduced complications, and improved satisfaction with the transition process. The findings will provide valuable insights into the impact of nurse-led interventions on the care transition for CHD patients, potentially improving both caregiver and patient outcomes.
